### Metabolomics:

Metabolic datasets will be analysed using principal component analysis (PCA) and orthogonal partial least-squares analysis (O-PLS). The metabolic and microbial data will also be analysed in relation to response measurements such as BMI, gut hormone levels and etc. using O-PLS regression analysis and Bayesian approaches. A range of statistical methods will be optimised and applied to the data to identify weight loss and T2DM-associated microbiota and metabolites.

### Health Economics:

The economic health analysis will be conducted following the NICE Reference Case, which includes the use of QALYs as the measure of health outcome, and adoption of an NHS and Personal Social Services perspective for costs (Guide to the methods of technology appraisal 2013, <http://publications.nice.org.uk/pmg9>). Both costs and QALYs will be discounted at the recommended rate of 3.5% per year.

**Within trial analysis:** EQ-5D health states will be scored using the UK social tariff to give a utility values at each time point (-2 weeks, 10 days, 1, 3, 6, 11.5, and 23 months). QALYs will be estimated for each patient using an area-under-the curve approach.

The cost of the EndoBarrier intervention, the lifestyle intervention, and other related health and social care will be estimated from resource use data. Unit costs for the included services will be obtained from standard national sources (BNF for drug prices, Department of Health Reference Costs for investigations, procedures and outpatient visits, PSSRU estimates for other primary and community health and social services). Total costs will be estimated for each patient over the 24-month trial period.

|                                                                                   |                                                                                                  |                                           |                                                             |                                                  |
|-----------------------------------------------------------------------------------|--------------------------------------------------------------------------------------------------|-------------------------------------------|-------------------------------------------------------------|--------------------------------------------------|
| [figure not shown] | Title:
EndoBarrier TM
Gastrointestinal Liner
Diabetes Trial | Protocol No:
Version 5.0 | Sponsor:
Imperial College
London | Date:
5th March 2018 |
|-----------------------------------------------------------------------------------|--------------------------------------------------------------------------------------------------|-------------------------------------------|-------------------------------------------------------------|--------------------------------------------------|

Patient-level cost and QALY estimates will be combined to estimate an Incremental Cost Effectiveness Ratio (ICER) for the Endobarrier device compared with standard medical therapy over the 24 month trial period. The analysis will combine multiple imputation to account for missing EQ-5D and resource use data with bootstrap regression to estimate mean cost and QALYs for the two patient groups. Missing data is often a particular problem for economic analysis, even in studies with good follow-up of primary endpoints, as area under the curve approach requires data from multiple time points. A bootstrap regression approach will be used to account for non-normal distributions of cost data, to adjust for baseline differences in utility or other patient characteristics, and to allow for correlations between costs and QALYs.

**Cost-effectiveness modelling:** A decision analytic model will be developed to estimate clinical outcomes, QALYs, and costs beyond 24 months. The time horizon for the modelling will be for the remainder of the patient's predicted lifetimes, as recommended in modelling guidelines.

Before commencing this modelling exercise, we will review existing economic decision models for weight loss interventions for people with Type 2 diabetes. There are several validated diabetes models that have been compared and validated against external data. These models take baseline information about patients' risk factors (demographic, behavioural and metabolic biomarkers), predict how these risk factors change over time, and hence simulate the incidence of diabetic complications, survival, quality adjusted survival, healthcare usage and costs. Most diabetes models rely on the UKPDS Risk Engine to reflect the relationships between the risk factors. This series of equations is based on a multivariate analysis of data from the UKPDS clinical trial, adapted to reflect risk in a general T2DM population. For example, the UKPDS Outcomes Model is a computer simulation model the lifetime benefits of diabetes-related interventions for use in economic evaluations. However, it is not clear that UKPDS-based models could adequately capture putative benefits from the EndoBarrier related to weight-loss or the remission of diabetes. The UKPDS risk engine does not include BMI as an independent predictor of diabetic complications; it does not include outcomes related to obesity but not to diabetes; and it cannot be used to model risk in patients in remission from diabetes.

A more recent model developed for the NICE Public Health guidance on preventing type 2 diabetes (Gillett et al. Prevention of type 2 diabetes: risk identification and interventions for individuals at high risk Economic Review and Modelling, ScHARR 2011, <http://www.nice.org.uk/guidance/index.jsp?action=download&o=57046>) may provide a more promising example of the type of model that we could use for the EndoBarrier evaluation. This uses an individual patient dataset from the Health Survey for England to characterise baseline profiles of risk factors within a representative population, and to estimate change in risk factors over time. Predictive algorithms from the QResearch primary care database (the QRisk2 and QDScore equations) are then used to predict the onset of diabetes and CVD. The model also allows for onset of other obesity-related diseases, including osteoarthritis and some cancers, and independent effects of BMI and diabetes on other-cause mortality and quality of life. It is then used to estimate the impact of five dietary interventions to prevent diabetes.

The review of this and other similar models will be used to identify possible model structures and sources of input parameters. The conceptual design of the model will be discussed and agreed

|                                                                                   |                                                                                                  |                                           |                                                             |                                                  |
|-----------------------------------------------------------------------------------|--------------------------------------------------------------------------------------------------|-------------------------------------------|-------------------------------------------------------------|--------------------------------------------------|
| [figure not shown] | Title:
EndoBarrier TM
Gastrointestinal Liner
Diabetes Trial | Protocol No:
Version 5.0 | Sponsor:
Imperial College
London | Date:
5th March 2018 |
|-----------------------------------------------------------------------------------|--------------------------------------------------------------------------------------------------|-------------------------------------------|-------------------------------------------------------------|--------------------------------------------------|

amongst the research team before programming commences. We anticipate that the model will take the form of an individual patient simulation, using either a discrete time or discrete event approach to simulate the onset of diabetes/obesity related complications, and hence QALYs and costs under alternative treatment strategies.

We will use data from the trial to provide estimates of the effect of the EndoBarrier compared with conventional management. In addition, we will review published systematic reviews and meta-analyses of bariatric surgery for similar a patient population. If recent evidence of sufficient relevance and quality is available, we will extend our model to include indirect comparisons with these other interventions. Other model parameters will be sourced from targeted literature reviews and routine data sources. The choice of software for the model will be made after specification of the conceptual design, but we have a similar model programmed in STATA, so this may provide a suitable platform for implementation. Before use, the model will be validated by an experienced health economist not involved in the development of the model. This will be done using a checklist developed by the Brunel Health Economics Research Group, which includes a range of suggestions for checking that a model is free from errors (verification) and that it is consistent with internal and external data (validation).

Probabilistic sensitivity analysis (PSA) will be used to estimate the impact of uncertainty over model parameters, and we will conduct a value of information (VOI) analysis to estimate the value of conducting further research. In addition, deterministic sensitivity analysis will be used to examine the impact of uncertainties over the model structure.

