### **Visit 6, 7, 9, 11**

The following will be performed:

- Body measurements including weight and waist circumference (5.5.8, 5.5.9)
- Vital signs (5.5.7)
- Routine chemistry and haematology (5.5.10)
- Adverse events (6)
- Medical history/medication changes (5.5.4)
- Dietitian follow up (5.5.3)
- Diabetologist/Endocrinologist diabetes review (5.5.1)
- Health Economics questionnaires (Visit 6 and 7 only) (5.5.4)
- Follow up appointment with gastroenterologist (Treatment arm only) (5.5.2)
- Preparation for EndoBarrier Removal (Visit 9 Treatment arm only) (5.5.2)
- EndoBarrier Removal (Visit 11 Treatment arm only) (5.5.2)
- Gastric and small bowel biopsies during EndoBarrier Explant (Treatment arm only) (5.5.2)

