### 5.5.12 Health Economics Questionnaires

Patients in both treatment arms will be asked to complete the health economics questionnaires at visits 3, 5, 7, 8, 10 and 14. These comprise the EQ-5D-5L questionnaire (<http://www.euroqol.org/eq-5d-products/how-to-obtain-eq-5d.html>) to assess health-related quality of life, and a bespoke questionnaire designed to collect information about patients' use of health and social care resources (for costing purposes).

The resource use questionnaire will be adapted from existing instruments including the CONSTRUCT (Williams J G, Russell I, Cohen D, et al. Comparison of infliximab and ciclosporin in steroid resistant ulcerative colitis: a trial CONSTRUCT, NIHR Health Technology Assessment

|                                                                                   |                                                                                                  |                                           |                                                             |                                                  |
|-----------------------------------------------------------------------------------|--------------------------------------------------------------------------------------------------|-------------------------------------------|-------------------------------------------------------------|--------------------------------------------------|
| [figure not shown] | Title:
EndoBarrier TM
Gastrointestinal Liner
Diabetes Trial | Protocol No:
Version 5.0 | Sponsor:
Imperial College
London | Date:
5th March 2018 |
|-----------------------------------------------------------------------------------|--------------------------------------------------------------------------------------------------|-------------------------------------------|-------------------------------------------------------------|--------------------------------------------------|

programme, <http://www.hta.ac.uk/project/1737.asp>;

<http://www.dirum.org/instruments/details/27>) and Chernak (Chernyak et al. BMC Health Services Research 2012, 12:303, <http://www.biomedcentral.com/1472-6963/12/303>) questionnaires and will ask patients to specify what services they have used since the previous assessment. The resource use questionnaire will include:

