- Medications for diabetes, weight loss, blood pressure, lipid control and cardiovascular disease;
- Primary care consultations (with GP, nurse or other healthcare professional);
- Hospital outpatient clinic visits (by specialty);
- A&E attendances (admitted/not-admitted);
- Inpatient stays and procedures;
- Investigations
- And use of other related community health and social services (e.g. chiropody).

Only services funded by the NHS or local authority personal social service departments will be included, as the health economic analysis will follow an 'NHS and PSS' perspective as recommended by NICE (Guide to the methods of technology appraisal 2013, <http://publications.nice.org.uk/pmg9>). Costs for private health and social care, out-of-pocket expenditure by patients, and 'indirect costs' per patient time will not be included.

In addition to the patient questionnaire, information will be collected in the CRF in order to cost the EndoBarrier intervention and the diet and exercise intervention. Information will be collected from hospital information systems and case notes, including:

- Routine assessments required before implantation and removal of the EndoBarrier;
- Disposables and staff time for the insertion and removal procedures, including day case and overnight stay if required; This information will adapted from other instruments (Resource Time Sheet page 194 of the HTA report for the MINuET trial: <http://www.journalslibrary.nihr.ac.uk/hta/volume-10/issue-40>);
- Treatment of any adverse events related to the procedures (additional inpatient stays, clinic visits and re-admissions);
- Dietitian time to deliver the diet and physical activity counselling and for telephone follow-up;
- Routine hospital follow-up and diabetes care;
- Hospital treatment for cardiovascular events or other complications of diabetes.

Costs related only to conduct of the trial (the outcome and mechanism assessments) will not be included, as these would not be required for routine implementation of the intervention. The cost of lifestyle coaching for both groups will be included because although this input should be similar for both groups, it is possible that attendance may differ.

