## 7.2 Early Discontinuation of Individual Subjects

Subjects may discontinue study treatment (EndoBarrier) for the following reasons:

- At the request of the subject.
- If the investigator considers that a subject's health will be compromised due to adverse events or concomitant illness that develops after entering the study.

Any subjects who withdraw from the study that have the device implanted will have the device removed as soon as it can be arranged. Subjects that have the device removed before Month 3 will return for the End of Treatment/Months 12 (visit 11). Subjects that have the device removed after Month 3 will return for the End of Treatment/Month 12 (visit 11), Month 15 (visit 12), Month 18 (visit 13) and Month 24 (visit 15) post explant follow-up visits.

All subjects (including both control and device arm) who withdrew from the study early (either prior or after their treatment started – visit 4), and where no follow-up visit has been agreed or arranged as part of the previous protocol version (V4.1), will be contacted over the phone by the study team to ask for their permission (verbal consent documented by the study doctor using a specific form filed in the medical records) to perform a short telephone consultation at Month 24 (equivalent to visit 15). Data collected during this visit will include:

- HbA1 (provided through their last routine appointment at their GP)
- Body weight in kg
- Adverse events (section 6)
- Medical history/medication changes (section 5.5.4)

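### No EQ-5D is taken between 11.5 and 23 months, at 24 months, or at the early-explant return visits, so the 24-month QALY difference is at risk of bias of uncertain size and direction

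*Protocol*

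**What the plan says.** Section 8.2 (Health Economics) scores EQ-5D to give "utility values at each time point (-2 weeks, 10 days, 1, 3, 6, 11.5, and 23 months", and states that "QALYs will be estimated for each patient using an area-under-the curve approach". For costs, "Total costs will be estimated for each patient over the 24-month trial period"; the incremental cost-effectiveness ratio (ICER) has the same 24-month horizon.

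These time points match the health economics row of Table 2: V3, V5, V6, V7, V8, V10 and V14. Section 5.4 agrees. Its list for visits 6, 7, 9 and 11 has "Health Economics questionnaires (Visit 6 and 7 only) (5.5.4", and its lists for V12, V13 and V15 have no such item. Section 5.5.12 differs at one visit: patients are asked to "complete the health economics questionnaires at visits 3, 5, 7, 8, 10 and 14", which leaves out V6.

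Planned removal is at V11, month 12 (section 5.5.2, Table 2). Under section 7.2, patients whose device is removed before Month 3 come back for V11 only. For the others, "Subjects that have the device removed after Month 3 will return for the End of Treatment/Month 12 (visit 11"), followed by V12, V13 and V15. The Month 24 telephone contact for early withdrawals collects HbA1c, weight, adverse events and medical or medication changes, but neither EQ-5D nor service use.

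Section 5.5.12 gives resource use two sources. The questionnaire "will ask patients to specify what services they have used since the previous assessment". Separately, "Information will be collected from hospital information systems and case notes, including" the insertion and removal procedures, treatment of procedure-related adverse events, routine hospital follow-up and treatment of complications.

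**The concern.** An area under the curve is only as good as its spacing around the times when utility may change. Here the longest interval contains the planned removal, and the year after removal rests on a single value at 23 months. Whatever happens to utility at and after explant is replaced by a straight line.

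The second gap is more serious. Section 8.1 allows for up to 30% early removal and assumes that these patients stay available for follow-up, and section 8.2 analyses by intention to treat. Yet the visits to which they are brought back do not ask the utility questions. The missingness is planned, occurs in one arm only, and is triggered by device removal, for which section 1.5 names bleeding, migration and pain as the commonest causes. Multiple imputation is planned, but no observed utility after an early removal would exist to inform it or to test its assumptions.

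QALYs and the incremental cost per QALY are secondary endpoints (section 2.5), and the trial's effect estimates also feed the lifetime model. The primary HbA1c analysis is not affected.

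**Working it through.** **Schedule.** Matching the section 8.2 times to Table 2: V3 (-2 weeks), V5 (10 days), V6 (1 month), V7 (3), V8 (6), V10 (11.5), V14 (23). All seven agree. The last interval is 23 - 11.5 = 11.5 months, and 11.5/24 = 47.9% of the horizon. The unmeasured tail is 1/24 = 4.2%. The SF-36 of the sub-groups (section 5.6.1) falls at visits 3, 8, 10 and 14, so it does not fill the gap.

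**Planned removal, relative error.** The documents give no utility values, so the paths below are assumptions. Let the device gain be u, constant to 11.5 months, and zero at 23 months.

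- Area to 11.5 months: 11.5/12 = 0.958u.
- Credited by the plan from 11.5 to 23 months: 0.5 x 11.5/12 = 0.479u.
- True area if the gain falls linearly from 11.5 months to zero k months after explant: 0.5 x (k + 0.5)/12.

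| k (months) | true area after 11.5 m | excess credited | true total | excess / true total |
|---|---|---|---|---|
| 1 | 0.063u | 0.417u | 1.021u | 41% |
| 3 | 0.146u | 0.333u | 1.104u | 30% |
| 6 | 0.271u | 0.208u | 1.229u | 17% |
| linear to 23 m | 0.479u | 0 | 1.438u | 0% |

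The percentages also depend on the path before 11.5 months. If the gain builds up linearly (0.479u to 11.5 months), the middle row becomes 0.333/(0.479 + 0.146) = 53%.

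**Planned removal, absolute error.** Let d be the arm difference at 11.5 months, assumed to be 0.02, 0.05 or 0.10.

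- Lost at once at 12 months: 0.479d - 0.042d = 0.4375d, or 0.009, 0.022 or 0.044 QALY in favour of the device.
- Held to 12 months, then linear to zero at 23: 0.479d - 0.5d = -0.021d, or -0.0004 to -0.002.
- Held to 18 months, then lost: the true area is 6.5/12 = 0.542u against 0.479u, so the gain is understated by 0.063u.
- Utility depressed on the device (d = -0.05) and restored at removal: -0.022, against the device.
- Unseen dip of 0.05 to 0.20 at removal lasting 0.5 to 3 months: 0.05 x 0.5/12 = 0.002 up to 0.20 x 3/12 = 0.05 QALY per device patient omitted.
- The 23 to 24 month tail: d/12 = 0.002 to 0.008.

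**Early removal.** 0.30 x 80 = 24 patients at most. On the listed visits, the last EQ-5D and the unmeasured share of 24 months are:

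- removal at 1.5 months: last value at 1 month, 23/24 = 96%;
- removal at 4.5 months: last value at 3 months, 21/24 = 87.5%;
- removal at 6.5 to 11 months: last value at 6 months, 18/24 = 75%.

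If their true utility were e below the imputed values from month r on, the device-arm mean would be too high by 0.30 x e x (24 - r)/12. For e = 0.02, r = 9 this is 0.008; for e = 0.10, r = 3 it is 0.053. If imputed values were too low by the same amounts, the sign would reverse.

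**The case against.** A reader might infer that resource use is not collected at all from 11.5 to 23 months, or that early-explant patients yield no cost data. The documents do not support either. The V14 form reaches back to the previous assessment, so on-schedule patients are covered to 23 months; the fair criticism is an 11.5-month recall. Hospital systems, case notes and the case report form supply procedure, adverse-event, follow-up and complication costs without the questionnaire, and medication changes are recorded at V11, V12, V13 and V15. What is lost is self-reported service use, such as primary and community care, after early removal and, for everyone, in month 24.

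A reader might also infer that the result is biased, and biased towards the device. That is not established. The protocol gives no utility path, a linear fade produces almost no error, and section 6.10 anticipates nausea, pain and bloating during the implant period, which could depress on-device utility and turn the error against the device. Nor can one say that imputation would fill failures from successes: the imputation model is commonly left to a statistical analysis plan, none is at hand, and completers' 23-month values are themselves off-device.

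The 30% is an upper bound; section 8.1 reports lower explant rates elsewhere. The one-month tail is small.

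These points narrow the matter to utility and to risk rather than proven bias. They do not close the gap across removal, and they do not supply any observed utility after early removal.

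**Conclusion.** The point stands for utility, and in part for self-reported service use. EQ-5D is absent for the 48% of the horizon that contains planned removal, absent at the 24-month end point, and absent by design after early removal for up to 24 of 80 device patients. The last is the weightiest, because later analysis cannot check what was never observed.

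The consequence is a risk of bias in the 24-month QALY difference, and hence in the ICER. Its size and sign depend on unknown utility paths. The overstatement is 17% to 41% of the true gain if a constant gain is lost within 6 to 1 months of removal; the error is about zero under linear fading; the gain may be understated if it persists into year 2 or if utility is depressed on the device. Misjudged imputation for early explants could move the device-arm mean by about 0.008 to 0.053 QALY for assumed utility errors of 0.02 to 0.10.

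The omission of V6 in section 5.5.12 is a separate, minor inconsistency. The change is worth making because it is cheap; it does not bear on the primary endpoint.

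**What to change.** - Give the EQ-5D-5L and the resource-use form at V11, V12, V13 and V15, and state that this includes the early-explant return visits in section 7.2. At V11, patients with planned removal should complete it before the procedure.
- Use V15 as the 24-month end point of the area under the curve and of the cost total.
- Amend Table 2 and sections 5.4, 5.5.12 and 8.2 together, and add V6 to section 5.5.12.

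The longest post-baseline interval falls from 11.5 to 5.5 months (6 to 11.5). If a difference d is lost at once at removal, the error falls from 0.4375d to 0.125d with V11 completed before removal (0.5/12 + 3/24 - 0.5/12), or to 0.104d with V12 as the next value after V10 (3.5/24 - 0.5/12). At d = 0.05 that is 0.022 down to 0.005 to 0.006 QALY. The recall period shortens as well.

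The cost is two short forms at up to four existing visits and a schedule amendment. There are two limits. Patients explanted before Month 3 return only at V11, so they gain one value at 12 months and nothing later. Visits already passed cannot be recovered: version 5.0 already arranges contact for patients who withdrew under the previous version.
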